## Interventions

### Explanation for the choice of comparators {6b}

The intervention, adjunctive low-dose corticosteroids, is being compared to the current standard of care treatment. While a placebo control could have been used, this would be difficult to implement in the context of a pragmatic trial. Having a mortality end point mitigates against any shortcomings arising from the lack of a placebo control group.

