### Sample size {14}

The primary hypothesis is that adjunct corticosteroid treatment will reduce mortality in the intervention arm by ~25% (relative measure). This is a conservative measure as the studies described in the background report relative risk reductions of between 33% and 61%. Observational data indicates 30% in-hospital mortality among based on data collected from CIN hospitals in the past one year and Kilifi County Hospital over a period of 5 years
^
24
^. We have made a conservative assumption that 30-day mortality in the control arm of the trial will be 20% and that 30-day mortality in the intervention arm will be 15%. Allowing for 5% loss to follow-up, a sample size of 1,090 patients per study arm (total 2,180 patients, ~ 390 deaths) will achieve statistical power of 85%, with a 2-sided type 1 error rate of 5%.

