### Recruitment {15}

Study clinicians will work with admitting clinicians at the outpatient departments, admissions area in the ward, and nursing teams at the medical wards to ensure they are informed of all patients admitted with respiratory illness. They will then screen these patients for eligibility for the trial and enrol those who provide written informed consent. A window period of 48 hours between admission and recruitment will be implemented to allow study clinicians adequate time to identify all eligible participants (
Table 2).

**Table 2. T2:** Summary of trial activities. This table summarises trial activities and procedures being conducted once a participant is recruited into the trial.

Study Day	Day of recruitment (Day 0)	During Hospitalization	After hospital discharge
Confirm eligibility	x		
Obtain written informed consent	x		
Randomization	x		
Patient issued with study number and a random treatment allocation	x		
Study Intervention (Standard care alone or standard care plus corticosteroid)	x	Daily for up to 10 days ^ a ^	x ^ a ^
Follow-up phone call			Day 14 Day 30
Data Collection	x	x	x
Adverse events		x	x
Blood samples ^ b ^	x	x ^ b ^	

^a^ If patient is discharged before 10 days, they will continue with corticosteroid medication as an outpatient until day 10.
^b^ Blood samples will only be collected from 100 randomly selected participants (50 in each arm) on day 0,1,2 and 3

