### Plans for collection, laboratory evaluation and storage of biological specimens for genetic or molecular analysis in this trial/future use {33}

Of the 10ml venous blood drawn from each patient for each time point, 0.5ml of the blood sample will be used to conduct a full blood count. The remaining sample will be used for whole blood transcriptome analysis and to obtain plasma and peripheral blood mononuclear cells (PBMCs) for immunology work.

A series of cellular and serological assays will be used to characterize the immunological and metabolic status of the participants. RNA will be purified, and libraries constructed and sequenced using the Novagene platform available at a collaborating laboratory in Kenya. The sequence data will be analyzed in R. EdgeR (
https://doi.org/10.1093/bioinformatics/btp616) will be used to determine genes differentially expressed between those who died and those who recovered following treatment with or without steroid administration to determine biomarkers predictive of the outcome of the treatment. The differentially expressed genes will also be used to determine, bioinformatically, before treatment immunological status associated with the outcome of the trial. The transcriptome profile from before, during and after treatment will also be compared to determine genes up- or down-regulated following treatment and the calculated fold change will be related to the outcome and used to understand the immunological response correlated with the outcome of the trial.

The stored PBMCs will be used to phenotype in detail the cellular immune status in the trial arms before, during and after treatment using flow cytometry. Specifically, the frequency of B-cells, CD4, CD8, Natural killer (NK) cells, gamma delta (
**γ** T cells) will be described. The CD4 T cell will be further categorized into Th1, Th2, Th17 as determined by expression of IFN-
**γ**, IL-4 and IL-17 through intracellular staining and flow cytometry. The cellular immune phenotype data along with blood count data will be correlated to the outcome of the trial and will facilitate interpretation of the whole blood transcriptome data obtained above. This data will be integrated with the phenotypic and transcriptomic data to understand immune and biological pathways associated with the outcome of the trial.

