## Statistical methods

### Statistical methods for primary and secondary outcomes {20a}

The primary analysis will be an intention to treat analysis in which we will compare outcomes between all patients randomized to the two study arms, irrespective of whether they receive their allocated treatment. For the primary outcome of 30-day mortality, we will use the unadjusted hazard ratio determined from Cox regression to estimate the mortality rate ratio between the treatment groups. If we detect any imbalances in potential confounders at baseline (such as age, sex, severity of illness, study site), then an adjusted Cox model will be used. If losses to follow-up do occur, patients will be censored at time of last assessment. Kaplan-Meier survival curves will be constructed to display cumulative mortality over the 30-day follow-up period.

In the per-protocol analysis we will exclude patients stopping or pausing the study medication at any time point and those withdrawn from the trial.

Complete case analyses will be used for secondary endpoints. For all secondary endpoints, we will calculate unadjusted and adjusted estimates of the effect size and corresponding 95% confidence intervals using linear, logistic, or cox proportional hazards regression as appropriate. All analysis will be done using R (Version 4.4.2, R Foundation for Statistical Computing: Vienna, Austria)

For the immunology outcome, omics data such as proteomic and transcriptomic data generated will be processed in the R programming language as described in section 33. To find genes/proteins whose mean response has significantly changed over the first 72 hours, the processed data will be fitted in a multinomial mixed model predicting the possible outcomes, adjusting for relevant baseline characteristics. The expected outcomes are, survived versus died in the treatment and placebo arms.

To understand the biological response associated with survival, induced/repressed by the treatment, functional analysis of the significant genes/proteins will be explored using R packages such as Clusterprofiller, GSVA and fgsea.

Integrative approaches will be used on the cellular phenotyping, proteomic, transcriptomic, metabolomic data to elucidate the biological processes promoted/repressed by corticosteroid treatment that are associated with survival that could be targeted with additional intervention

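### The immunology model in section {20a} is mis-specified for its stated aim: it predicts a vital-status-by-arm class that never changes within a patient, and it calls the standard-care arm placebo

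*Protocol article*

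**What the plan says.** The third secondary objective (Objectives {7}) asks how patients' immune and metabolic profiles, at baseline and as altered by treatment, relate to outcome in each arm. Table 2, footnote b, under Recruitment {15} sets the material: "Blood samples will only be collected from 100 randomly selected participants (50 in each arm) on day 0,1,2 and 3". Vital status is read once, at day 30 (Plans for assessment and collection of outcomes {18a}).

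Statistical methods {20a} sets out to find features whose mean level moves over 72 hours. For this, "the processed data will be fitted in a multinomial mixed model predicting the possible outcomes, adjusting for relevant baseline characteristics". The classes follow: "The expected outcomes are, survived versus died in the treatment and placebo arms". Features declared significant then feed the functional analysis.

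The comparator is described differently elsewhere. Explanation for the choice of comparators {6b} states: "While a placebo control could have been used, this would be difficult to implement in the context of a pragmatic trial". Intervention description {11a} defines the control as standard care, and Implementation {16c} and Who will be blinded {17a} describe an open-label trial.

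The specimens section {33} plans further analyses for the same objective: edgeR comparing patients who died with those who recovered, with or without steroid; pre-treatment status against outcome; and fold change against outcome. On timing it says: "The transcriptome profile from before, during and after treatment will also be compared". It extends the approach to proteins and metabolites.

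**The concern.** The protocol names a specific model here, so this is not detail left to an analysis plan. The model does not match the question in four ways.

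- **Direction.** A change in mean expression over time needs expression on the left-hand side, with time and arm on the right. Section {20a} puts the clinical class on the left.
- **Arm inside the response.** Vital status has only two values, so a multinomial model makes sense only if the classes are vital status crossed with arm, which gives four. Arm is assigned by randomisation and is not an outcome to predict.
- **No variation within patient.** Arm is fixed and vital status is read once, so a patient has the same class at every sample. Changes between samples cannot explain a response that does not change.
- **Label.** There is no placebo arm.

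The list of significant features drives the pathway analysis, so a model with no stable fit, or one that treats repeated samples as separate patients, would carry through to the biological conclusions.

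**Working it through.** **1. Check that the mortality rates are read correctly.** Sample size {14} assumes 20% (control) and 15% (intervention), 85% power, two-sided 5% and 5% loss.

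- n per arm = [1.960 × √(2 × 0.175 × 0.825) + 1.036 × √(0.20 × 0.80 + 0.15 × 0.85)]² / 0.05² = 1,036 after rounding up.
- 1,036 / 0.95 = 1,091, against the stated 1,090. Reproduced.
- Deaths with no loss: 1,090 × (0.20 + 0.15) = 381.5, against about 390 stated, a difference of about 2%.

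**2. Expected deaths in the sub-study.** The protocol gives no figure, so these are derived.

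- At the protocol's rates: 50 × 0.20 = 10 and 50 × 0.15 = 7.5, total 17.5. Binomial 95% ranges are 5 to 16 (control), 3 to 13 (intervention) and 10 to 25 (total).
- The same section also reports: "Observational data indicates 30% in-hospital mortality". Taking 30% as control mortality with the same 25% relative reduction (0.30 × 0.75 = 0.225) gives 15 + 11.25 = 26.25.

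**3. Can a patient random effect be estimated?** As a simplification, take two classes (died or survived), 100 patients, 18 deaths, no covariates and four identical rows per patient. With random-intercept SD σ, a patient who died contributes the average of p⁴ over the random effect, and a survivor the average of (1 − p)⁴, where logit p = μ + σz. The log-likelihood, maximised over μ, is:

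| σ | log-likelihood |
|---|---|
| 0.01 | −188.5 |
| 2 | −100.3 |
| 10 | −57.3 |
| 100 | −48.1 |
| 500 | −47.3 |

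The upper bound is 18 × ln 0.18 + 82 × ln 0.82 = −47.14. The curve keeps rising towards it, so σ has no finite maximum. Crossing the classes with arm leaves the rows of a patient just as identical.

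**4. What if there is no patient effect?** With, say, a hospital effect only, four rows from one patient count as four independent observations. In the limiting case where the marker also barely changes between samples, standard errors are too small by a factor of √4 = 2.

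**5. What precision is available for the by-arm question?** Assume one row per patient, a standardised marker, no covariates and an effect near the null. The standard error of the log odds ratio per SD is about 1/√(n·p·q).

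- Control: 1/√(50 × 0.20 × 0.80) = 0.354. Intervention: 1/√(50 × 0.15 × 0.85) = 0.396.
- Difference between arms: √(0.354² + 0.396²) = 0.531.
- Ratio of odds ratios detectable with 80% power at a single two-sided 5% test: exp[(1.960 + 0.842) × 0.531] = 4.4.
- In the 30% scenario the standard error is 0.458 and the detectable ratio 3.6.

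These are figures for one test. Correction over many features makes them larger.

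**The case against.** The strongest reply is that the objective does not depend on this one sentence. Section {33} plans edgeR, baseline-status and fold-change analyses against outcome, and edgeR takes expression as the response. That stands. A reader might infer from the faulty model that the secondary objective cannot be answered, but the documents do not support this.

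Second, section {20a} says only *mixed* and never names the patient as the grouping factor. With 20 hospitals, a site effect is possible. One row per patient (a baseline value or a fold change) is also possible and removes the identifiability problem; within-arm contrasts of death and survival could then be formed from the four-class logits. This is fair, but it does not rescue the sentence as written. With a site effect only, repeated samples are treated as independent. With one row per patient, the model still does not estimate a change in mean expression.

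Third, a reader might set the number of coefficients against the number of deaths and conclude that the model will not converge. The protocol does not fix the number of predictors, and a four-class model also uses the roughly 82 survivors. Few deaths limit precision under any model, including the replacement proposed here.

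Fourth, *placebo* is one wrong word, and *after treatment* in section {33} is loose wording. The comparator and the sampling times are plain elsewhere, and {20a} confines its aim to 72 hours. Both are wording corrections. A reader might infer that an end-of-treatment contrast is planned without samples, but the statistical section contains no such contrast.

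**Conclusion.** The concern holds for the model in section {20a}. Its response should be an explanatory factor, includes the randomised arm, and is constant over a patient's samples. On the repeated samples it therefore either has no finite patient-level variance or ignores the correlation. It also mislabels the control arm.

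The secondary objective remains partly served by section {33}, with low precision: about 17.5 expected deaths among 100 patients, or about 26 under 30% control mortality. The death counts assume that the sub-study patients die at the main-trial rates. The identifiability result rests on a two-class simplification without covariates, and the detectable ratios on the assumptions in step 5.

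The matter should be corrected, but it is confined to the sub-study. The primary analysis, the sample size and the mortality secondary outcomes are untouched.

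**What to change.** In section {20a}:

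- Model each feature as the response, using a linear or count mixed model, or limma/edgeR with patient blocking. Include time, arm and arm-by-time, a patient random effect and false-discovery-rate control, with all sampled patients.
- In a separate model with one row per patient, relate the baseline level and the 0 to 72 hour change to 30-day death, with few covariates. Include a marker-by-arm term labelled exploratory. For change scores, use a landmark at the last sample, so that only patients still alive then contribute; this leaves fewer deaths than step 2 gives.
- Replace *placebo* with *standard care*.

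In section {33}, align the *after treatment* wording with sampling up to 72 hours, and state how its analyses and those of {20a} divide the objective.

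The cost is revised wording and a standard pipeline in the same software, with no new samples. The downside is that the by-arm association with survival becomes exploratory. Recruitment has ended, so if any omics results have already been seen, the change should be dated and declared.

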The stored plasma will be used to characterize, at proteomic and metabolic level, the global immune and metabolic status before treatment and changes induced following treatment. Luminex platform will be used to quantify specific cytokines using commercial kits such as the 34-plex human ProcartaPlex from Thermo Fisher Scientific that contain multiple targets that have been associated with Pneumonia including SARS-CoV-2 related pneumonia. We will also quantify a range of growth factors such as Insulin-like growth factor 1 (IGF-1)
^
25
^, IGF binding proteins such as IGFBP1-6 and GDF-15
^
26
^ that have been shown to influence host survival under adverse conditions. 

In addition to the targeted approach, untargeted mass spectrometry approach will be used, a facility that is available at KEMRI-CGMRC. Using this approach, we identified upregulation of IGF-1 binding protein 2 (IGFBP2) that functionally inhibits IGF- and inflammation
^
27
^ to be associated with the risk of early death in sick malnourished children. Both before and after treatment samples for each participant will be subject to targeted and untargeted analysis and analysed as described for the whole transcriptome data to identify protein/metabolite biomarker(s) predictive of the outcome of the trial and the immunological and metabolic processes relevant to the outcome. Samples will be stored for future use according to KEMRI guidelines and consent for this will be sought from the participants sampled.

Samples will be stored for future use according to KEMRI guidelines and consent for this will be sought from the participants sampled.

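### As worded, the pathway analysis gives significance-filtered genes/proteins to fgsea and GSVA, which need all measured features; state the input for each tool

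*Protocol article*

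**What the plan says.** Section {20a} of the protocol article describes two linked steps for the omics data. The first is a selection step, a multinomial mixed model used "To find genes/proteins whose mean response has significantly changed over the first 72 hours". The second takes the selected features as its object: "functional analysis of the significant genes/proteins will be explored using R packages such as Clusterprofiller, GSVA and fgsea". Its stated purpose is to understand the biological response that is associated with survival and induced or repressed by treatment. A following paragraph plans integrative approaches across the cellular, proteomic, transcriptomic and metabolomic data, with no significance filter mentioned.

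Section {33} gives the data sources:
- **Whole-blood RNA:** "The remaining sample will be used for whole blood transcriptome analysis", alongside plasma and cell preparations.
- **Targeted proteins:** "Luminex platform will be used to quantify specific cytokines using commercial kits such as the 34-plex human ProcartaPlex", described as kits that "contain multiple targets that have been associated with Pneumonia including SARS-CoV-2 related pneumonia", plus a list of growth factors.
- **Untargeted proteins and metabolites:** "In addition to the targeted approach, untargeted mass spectrometry approach will be used".

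The same section says that the targeted and untargeted plasma data will be analysed in the way described for the transcriptome.

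The sub-study size is in the footnote to Table 2: "Blood samples will only be collected from 100 randomly selected participants (50 in each arm"), at four time points.

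**The concern.** The three named packages do not take the same input.
- **fgsea** asks whether the members of a set lie towards one end of a ranking of all measured features. Features that did not reach significance are part of the comparison.
- **GSVA** computes a score per sample and set from the whole expression matrix.
- **Over-representation testing** (in the first package named) is the one method that properly starts from a list of significant features. Its result depends on the background chosen.

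The sentence names the significant features as the input for all three. Followed literally, it removes the comparison that fgsea and GSVA rely on, and it discards sets whose members each move a little in the same direction. Those methods are usually chosen to find exactly that pattern. At stake is the pathway reading of the immunology secondary outcome, from which the article hopes to identify processes for further intervention.

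A second, conditional issue concerns the targeted panel. Its analytes were picked for their link to pneumonia. Testing a few of them for over-representation against the whole genome would therefore largely report the content of the kit.

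**Working it through.** The article gives no figure for the pathway analysis, so there is none to reproduce. The mortality assumptions come from section {14}. They do reproduce its sample size: 20% v 15%, 85% power and two-sided 5% give 1,036 per arm, and 1,036/0.95 = 1,091 against the stated 1,090.

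**1. Expected deaths in the sub-study.** 50 × 0.20 + 50 × 0.15 = 17.5. With the 30% observational in-hospital mortality that section {14} also cites, and a 25% relative reduction, the figure is 50 × 0.30 + 50 × 0.225 = 26.25.

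**2. How hard the filter is for died v survived.** Assumed, not in the article: 15,000 independent genes and a Benjamini-Hochberg false discovery rate of 5%.
- Standard error of a standardised difference: √(1/17.5 + 1/82.5) = 0.263.
- For a single gene to pass alone it needs p < 0.05/15,000 = 3.3 × 10⁻⁶, that is |z| > 4.65, or an observed difference of 4.65 × 0.263 = 1.22 SD.
- A true shift of 0.2, 0.3 or 0.4 SD moves z by only 0.76, 1.14 or 1.52.
- At 0.4 SD, the expected number of genes passing in a 100-gene set is about 100 × P(Z > 4.65 − 1.52) = 0.09.

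**3. Full list v significant list, first simulation.** The assumptions are those of step 2, with one 100-gene set shifted by 0.2 to 0.4 SD. A rank test (Mann-Whitney, standing in for fgsea) was judged at 0.05/50, with 300 runs per shift.

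| Input | Set detected |
|---|---|
| All genes, ranked | 100% |
| Significant genes only | 0% |

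On average only 0.06 to 0.11 genes of 15,000 passed the filter, so there was almost nothing to analyse.

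**4. Full list v significant list, second simulation.** The filter in section {20a} is on change over 72 hours, which many genes may pass. A second scenario therefore assumed 8,000 genes with 20% strongly changed, a 50-gene set with each z shifted by 1, and a filter at |z| > 2.8. The number of set members expected to survive is about 50 × P(Z > 1.8) = 50 × 0.036 = 1.8. Over 60 data sets with a weighted running-sum statistic, the set was detected in 100% from all genes and in under 2% from significant genes.

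**5. Panel content and background.** Assumed: a 20,000-gene genome and all 34 targets in an immune term of K genes. If any 5 analytes are called significant, even by chance, all 5 lie in the term, and p ≈ (K/20,000)⁵.
- K = 600: 0.03⁵ = 2 × 10⁻⁸.
- K = 200 and K = 1,500: 1 × 10⁻¹⁰ and 2 × 10⁻⁶.
- With the 34 analytes as background, p = 1.

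Relaxing the assumption, let 25 to 30 of the 34 lie in a 700-gene term and 5 to 10 be picked at random. Two hits already give p < 0.05 against the genome (0.011 with 5 picked, 0.046 with 10). The chance of a false immune enrichment is then about 99 to 100% with a genome background, and 0 to 2.6% with the panel as background.

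**The case against.** The strongest reply is that the sentence is looser than a literal reading makes it. It does not say that only significant features will be used, the step is exploratory, and the packages are examples. Naming fgsea and GSVA is itself some evidence that full-list methods are meant. The integrative analyses pursue the same aim with no stated filter. This stands as a limit: the documents do not show that pathway work is confined to the significant list, or that real shifts will be lost. It does not remove the mismatch, because the input is stated rather than left open, and it is the wrong input for two of the three tools.

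A reader might also infer that the plan will produce false immune enrichment. The documents do not support that. It would need a genome-wide background, and none is fixed; an article may leave that detail to the full protocol or analysis plan. Nor does the article say that transcripts and panel proteins are pooled into one list. The argument does not touch the RNA sequencing or the untargeted mass spectrometry, and the 34-plex kit is only an example. What stands is that section {33} puts the targeted analytes within the same analysis, so the caution has an object.

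Finally, every simulation input other than the death counts is assumed, and treating genes as independent flatters the full-list result. That is correct, and it is why only the direction is used.

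**Conclusion.** The point holds as a mismatch between the stated input and the methods named. Only over-representation testing properly takes a significant list; fgsea and GSVA need all measured features. The consequence is conditional on the sentence being followed as written. In that case a sub-study of 100 people with about 17 to 18 expected deaths (about 26 at the higher mortality) may have few features to work with on the survival contrast, and modest coordinated shifts can be missed. The contrast of 100% with 0 to 2% is an illustration under assumed inputs and not an estimate for this trial.

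For the targeted panel the conclusion is a caution: nearly automatic immune enrichment if the background is genome-wide, and none of note if the panel is the background. The importance is minor. It concerns an exploratory part of one secondary outcome and leaves the primary mortality analysis untouched.

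**What to change.** Replace the sentence in section {20a} with wording to this effect:
- fgsea is run on all features measured on each platform, ranked by the model statistic for the contrast of interest: treatment effect, survival association, or their interaction. Ranking only by the arm-by-time statistic would drop the association with survival that the section sets out to study.
- GSVA is run on the full normalised matrix of each platform.
- Over-representation testing of the significant list is supplementary, with the features measured on that platform as background.
- For the targeted Luminex and growth-factor analytes, either the panel is the background or the analytes are reported individually.

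The cost is a few lines of text. The packages, samples and data stay the same.
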